## Abstract

**Background:**

Since birth, during the exploration of the environment to interact with objects, we exploit both the motor and sensory components of the upper limb (UL). This ability to integrate sensory and motor information is often compromised following a stroke. However, to date, rehabilitation protocols are focused primarily on recovery of motor function through physical therapies. Therefore, we have planned a clinical trial to investigate the effect on functionality of UL after a sensorimotor transcranial stimulation (real vs sham) in add-on to robot-assisted therapy in the stroke population.

**Methods:**

A randomised double-blind controlled trial design involving 32 patients with a single chronic stroke (onset > 180 days) was planned. Each patient will undergo 15 consecutive sessions (5 days for 3 weeks) of paired associative stimulation (PAS) coupled with UL robot-assisted therapy. PAS stimulation will be administered using a bifocal transcranial magnetic stimulator (TMS) on the posterior-parietal cortex and the primary motor area (real or sham) of the lesioned hemisphere. Clinical, kinematics and neurophysiological changes will be evaluated at the end of protocol and at 1-month follow-up and compared with baseline. The Fugl-Meyer assessment scale will be the primary outcome. Secondly, kinematic variables will be recorded during the box-and-block test and reaching tasks using video analysis and inertial sensors. Single pulse TMS and electroencephalography will be used to investigate the changes in local cortical reactivity and in the interconnected areas.

**Discussion:**

The presented trial shall evaluate with a multimodal approach the effects of sensorimotor network stimulation applied before a robot-assisted therapy training on functional recovery of the upper extremity after stroke. The combination of neuromodulation and robot-assisted therapy can promote an increase of cortical plasticity of sensorimotor areas followed by a clinical benefit in the motor function of the upper limb.

**Trial registration:**

ClinicalTrials.gov NCT05478434. Registered on 28 Jul 2022.

## Administrative information

Note: the numbers in curly brackets in this protocol refer to SPIRIT checklist item numbers. The order of the items has been modified to group similar items (see http://www.equator-network.org/reporting-guidelines/spirit-2013-statement-defining-standard-protocol-items-for-clinical-trials/).

## Introduction

### Background and rationale {6a}

Up to 80% of stroke survivors have upper limb (UL) impairments early after stroke and a few of these demonstrate complete functional recovery after 6 months from the stroke event [1]. Impairment of the UL is one of the factors that contribute to reducing the overall quality of life impacting significantly social participation and the odds of return to professional activities [2]. The impairment of the UL is due to motor and sensory alteration that could compromise the sensorimotor integration, which is a complex process in the central nervous system which produces task-specific motor output based on selective and rapid integration of sensory information from multiple sources [3]. Specifically, sensory and motor signals are integrated by specific brain circuits during goal-directed behaviour and active exploration of the sensory environment [4]. The posterior parietal cortex (PPC) is a potential circuit where sensorimotor integration could occur during an active somatosensorial task [4]. Indeed, PPC is a site of massive confluence of visual, tactile, proprioceptive and vestibular signals [5]. This area may be involved in transforming information about the location of targets in space, into signals related to motor intentions [6]. This process likely occurs through parietal-motor connections, which are known to be involved in the transfer of relevant sensitive information for planning, reaching and grasping. Sensorimotor integration can be explained by anatomical cortico-cortical connections between PPC and the primary motor area (M1) by bundles of the superior longitudinal fasciculus [7]. Indeed, these mechanisms are not fixed but susceptible to rapid adaptations and modulation, through Hebbian-like plasticity mechanisms [8], in different populations of postsynaptic neurons. Recently, it has been found that paired associative stimulation (PAS) of PPC and M1, by means of bi-focal TMS, can modulate M1 excitability [9]. This information reinforces the hypothesis that modulation of PPC-M1 connectivity can be used as a new approach to modify motor excitability and sensorimotor interaction [8]. Moreover, Hebbian plasticity is a key factor of learning-dependent mechanisms for recovery of the UL after stroke [10].

Parallel, in the past decades, robotic therapy often focuses on increased strength and joint movement. Robot-assisted training can induce a plastic reorganisation at the muscular afferents, spinal motor neurons, interneuron system and beyond and facilitates neural plasticity and motor relearning through goal-oriented training programme. This technology can assist patients in their movements and of generating a biomechanical biofeedback based on measurements of movement. This biofeedback can sometimes be referred to as augmented feedback, providing the user with additional information, above and beyond the information that is naturally available to them as opposed to the sensory (or intrinsic) feedback [11]. The augmented feedback has greater clinical effects than sensory feedback and generates a facilitation in the neural plasticity after a brain injury. The robotics device allows to train patients in an intensive, task-oriented and top-down therapy way, increasing patients’ compliance and motivation. The cognitive top-down stimulation is allowed by the introduction of visual feedback performed through exergaming [12]. In addition, by using computer-assisted devices for regaining UL function, the robot can easily apply new constraints, to optimise the required movement pattern. Specifically, the robotic exoskeleton can assist the paretic UL in a large 1D, 2D or 3D environment by promoting movement [13]. Therefore, the complexity of a motor task can be controlled for more precisely with robotics than in conventional treatment approaches. Recently, the development of new intervention strategies has been proposed combining neurostimulation of a target brain area with neurorehabilitation, such as physical therapy or virtual reality [14]. Although both TMS and robot-assisted therapy (RAT) have shown individually promising effects in UL recovery after a stroke [15–17], their combination has not been tested to date. In detail, a paired stimulation of two interconnected areas of the cerebral cortex has not been combined with a specific and precisely controlled rehabilitation through robotic exoskeleton. The use of robot-assisted training may also drastically reduce the bias induced by neurorehabilitation administered by different physiotherapists, which intrinsically can undergo greater discrepancies between exercises. The possibility of a robot to measure body movement, through its embodied motion sensors, allows for the recording of data related to UL performance, also providing monitoring of motor training during the trials.

## Objectives {7}

We expect that the neurostimulation of the PPC-M1 network combined with robot-assisted training (experimental group) may be more effective than sham stimulation (control group). The assumption is that the PAS promotes a direct modulation of cortical plasticity while the robot-assisted exergaming provides only an indirect stimulation of circuits involved in grasp and reaching movements.

## Trial design {8}

A randomised, parallel groups, double-blind, two-arms, sham-controlled trial will be implemented to investigate the effects of the PPC-M1 PAS in add-on to RAT. Neurologists, PM&R, engineers, psychologists and physiotherapists were involved in the study design. No patient or public participation was foreseen.

## Methods: participants, interventions and outcomes

### Study setting {9}

All procedures will be performed in the clinical and behavioural neurology department and in the cognitive, motor and neuroimaging neurorehabilitation department of the Santa Lucia Foundation Hospital. Specifically, the brain stimulation will be administered in the Non-Invasive Brain Stimulation Unit (NIBSU) and the RAT in the rehabilitation unit 6.

### Eligibility criteria {10}

All patients with single ischemic stroke in the area of the middle cerebral artery in the chronic phase (> 180 days to stroke) that reported a severe-to-mild UL hemiparesis (Fugl-Meyer scale score < 52) will be screened for inclusion (Fig. 1). Inclusion criteria were as follows: (1) first ever chronic ischemic stroke; (2) hemiparesis due to left or right subcortical or cortical lesion in the territory of the middle cerebral artery; and (3) residual UL impairment (FMA-UE < 52). Exclusion criteria: (1) patients older than 80 years; (2) history of seizures; (3) severe general impairment or concomitant diseases (e.g. Parkinson’s disease, multiple sclerosis); (4) treatment with benzodiazepines, baclofen, antidepressants and botulinum toxin; (5) intracranial metal implants; (6) cardiac pacemaker; (7) pregnancy status; (8) orthopaedic contraindications for UL (e.g. shoulder periarthritis, Dupuytren’s disease); (9) UL pain; (10) cognitive impairment (MMSE score < 23); (11) and presence of unilateral spatial neglect (evaluated through a clinical and functional assessment).

**Fig. 1 Fig1:**
[figure not shown]
Inclusion flowchart

### Who will take informed consent? {26a}

Before starting the trial, the principal investigator or a sub-investigator will explain the experimental procedure and collect a written informed consent signed from each participant.

### Additional consent provisions for collection and use of participant data and biological specimens {26b}

In the consent form, participants will be requested to allow the utilisation of their data in accordance with local privacy policy. In the event of drop-out, they will be requested to indicate willingness to allow the utilisation of acquired data. Additionally, participants will be asked for their consent to share pertinent data with the sponsors. This trial does not involve the collection and storage of biological samples.

### Interventions

#### Explanation for the choice of comparators {6b}

We choose a combined placebo stimulation plus active-control robot-assisted comparator to reduce the bias of perceived allocation. Specifically, both groups will receive, real (Experimental group—Exp) or sham (Control group (Ctrl)), cortico-cortical PAS immediately before each session of RAT training. The Ctrl group received the same RAT protocol of the Exp group. Each participant will undergo 15 consecutive sessions (5 times a week, for 3 weeks) of PPC-M1 PAS (real or sham) in add-on to 30 min of RAT in a supervised clinical setting.

#### Intervention description {11a}

##### Transcranial magnetic stimulation procedure

A bifocal TMS will be applied to repeatedly activate the connection between the PPC and the M1 of the lesioned hemisphere [6]. Paired-pulse stimulation protocol, with 5-ms interstimulus interval between the two pulses, will be done through two Magstim 200 stimulators connected in a bi-stim mode. To stimulate the PPC area (90% rMT), the centre of the coil will be positioned over P4 (10–20 EEG system) tangentially to the skull with the handle pointing downward and slightly medial (15°) to induce a posterior anterior-directed current in the underlying cortical tissue. To stimulate the M1 area (120% rMT), the coil will be placed tangentially to the scalp at a 45° angle to the midline to induce a posterior-anterior current flow across the central sulcus. Differently from the Exp group, the Ctrl group will receive sham stimulation with a coil inclination of 90° with respect to the scalp.

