### Data collection and management

#### Plans for assessment and collection of outcomes {18a}

Clinical, instrumental and neurophysiological evaluation will be assessed at baseline (T0); after the 3 weeks of treatment (T1); and after 7 weeks from the baseline as a follow-up—4 weeks from the end of the treatment—(T2).

Demographics data (i.e. age, gender, lesion site) will be acquired through clinical documentation provided during the screening procedure. All collected data will be stored in an online data sheet protected with a password. To promote data quality, all raters were specifically trained in the administration of the clinical scales and in kinematics evaluation.

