##### Neurophysiological assessment

We will use 120 single pulses for each area (M1 and PPC bilaterally) during electroencephalographic recordings (EEG) to measure changes in the local activity of the stimulated area and on its cortico-cortical connections. The combined use of TMS-EEG represents one of the most promising approaches in the investigation of brain dynamics, in terms of cortical activity and connectivity. Indeed, EEG can record the postsynaptic potentials generated by the TMS-evoked neuronal depolarisation providing direct information on the neurophysiological state of the stimulated area and on its connections over the cortex. Recently, the main components of TEPs that can be detected in the first 200 ms after the probing TMS pulse have been put in relation with the activity of GABAergic interneurons [28].

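### The PPC coil site is fixed at P4, on the right, although the target is the lesioned hemisphere and left-sided lesions are eligible

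*Protocol article*

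**What the plan says.** The section on the TMS procedure (Intervention description {11a}) opens with the target: "A bifocal TMS will be applied to repeatedly activate the connection between the PPC and the M1 of the lesioned hemisphere". The abstract's Methods paragraph names the same hemisphere, ending the description of the two stimulated areas with "the primary motor area (real or sham) of the lesioned hemisphere".

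The TMS section then gives the coil positions. For the PPC, "the centre of the coil will be positioned over P4", with a reference to the 10–20 EEG system. For M1, "the coil will be placed tangentially to the scalp", with an angle to the midline but no side and no electrode label.

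Eligibility criteria {10} admit "hemiparesis due to left or right subcortical or cortical lesion in the territory of the middle cerebral artery". Interim analyses {21b} lists lesion side among the factors to be balanced if the groups turn out unequal, so the investigators expect it to vary between patients.

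The dose is given under Explanation for the choice of comparators {6b}: "Each participant will undergo 15 consecutive sessions (5 times a week, for 3 weeks) of PPC-M1 PAS (real or sham"), followed by robot-assisted therapy that is the same in both groups.

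**The concern.** The stimulation is meant to strengthen the connection between parietal and motor cortex within the damaged hemisphere. The background section grounds this in anatomical links between the two areas. Because robot-assisted therapy is common to both arms, this pairing, real or sham, is all that the randomised comparison tests.

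The M1 instruction names no side, so it can follow the lesion. The PPC instruction names a right-sided site and, as written, cannot. Followed literally, it would pair right PPC with left M1 in real-arm patients with left lesions, while right-lesion patients would receive the intended within-hemisphere pairing. The experimental arm would then contain two different treatments, separated by lesion side, and only one of them would be the treatment the trial sets out to evaluate.

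If practice followed the lesion, only the wording is at fault. Even so, someone replicating the treatment, or auditing its delivery against this article, would have to choose between two instructions that disagree.

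**Working it through.** The article gives no figure to reproduce here. The check is one of consistency between target, population and site, followed by a count of what could be affected.

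**Inputs from the article**
- Target: PPC and M1 of the lesioned hemisphere (TMS procedure; abstract, Methods).
- Population: left or right lesions (Eligibility criteria {10}).
- PPC site: P4, unconditional (TMS procedure).
- Planned sample: 32 patients (Sample size {14}).
- Dose: 5 sessions a week for 3 weeks (section {6b}).

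**Input from general convention, not from the article:** in the 10–20 system even numbers denote the right side and odd numbers the left. P4 is thus right parietal, and its left counterpart is P3.

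**Comparison by lesion side**

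| Lesion | Target PPC | Named PPC site | M1 (no side named) | Site agrees with target? |
|---|---|---|---|---|
| Right | Right | P4, right | Follows lesion: right | Yes |
| Left | Left | P4, right | Follows lesion: left | No |

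The three statements can all be true only for right lesions. Nothing else in the text resolves the left-lesion case. P4 occurs once in the text shown, P3 does not occur, and no phrase makes the electrode label depend on lesion side. The neurophysiological assessment does cover both sides ("We will use 120 single pulses for each area (M1 and PPC bilaterally"), but that is single-pulse stimulation during EEG to measure outcomes. It is not the paired treatment, and it names no electrode.

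**Count**
- Sessions per patient: 5 × 3 = 15.
- Planned sessions over both arms: 32 × 15 = 480.
- With k left-lesion patients, the site and target disagree in the text for 15 × k sessions: k = 0 gives 0, and k = 32 gives 480.

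The article does not state k, so this range is the whole of what is possible and says nothing about the likely number. Only real-arm sessions would bear on the treatment delivered. An effect on power cannot be derived: the article gives neither the left-lesion share nor an effect size, and the effect of stimulating the opposite PPC is unknown.

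**The case against.** The best defence is that the side rule is already stated, in the sentence that opens the same paragraph and again in the abstract. On that reading P4 is shorthand for the right-lesion case, and a trained operator would move the coil to the left for a left lesion. The article also condenses a fuller protocol, and Fig. 2, which depicts the stimulation protocol, is not available here; either may give the site by lesion side. If so, no treatment, endpoint, sample size or analysis changes, and the matter is one of wording.

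Much of this stands. The opening sentence most likely governs what was done, and no off-target stimulation is shown. It is also fair that a range covering every possible value measures nothing, and that the adherence note mentioned under {11c} is not said to record coil site, so existing records may not settle what was done.

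The defence does not remove the contradiction. Condensing explains detail that is left out, whereas here a specific site is given and it conflicts with the target stated just before it. The opening sentence states the aim, and the P4 sentence is the only PPC placement instruction in the text. Even a side-specific figure would leave that sentence wrong for left lesions.

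**Conclusion.** The point holds. As written, the intervention description places the PPC coil over the wrong hemisphere for one of the two eligible lesion sides. Confidence in the textual conflict is high. It rests on the article's own statements and on the convention that P4 is a right-sided site.

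The practical consequence is unknown. It depends on the number of left-lesion patients, which is not stated, and on whether operators followed the electrode label or the target, which the article does not show. A drafting slip is the likelier explanation. The correction should still be made, because the sentence defines the experimental treatment.

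**What to change.** In the TMS procedure section, give the PPC site by lesion side: P3 for left lesions and P4 for right lesions, with coil orientation mirrored, in both arms, the placement to be confirmed by the clinical team. The existing orientation wording refers to the midline and to a medial tilt, so it can serve either side.

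Then check that the site used since enrolment began on 19 August 2022 followed the lesion side. Do this for both arms alike, so that the check reveals no allocation. Lesion site is already collected: "Demographics data (i.e. age, gender, lesion site) will be acquired through clinical documentation provided during the screening procedure". Sessions are already recorded, but the article does not say that the stimulated side is noted. If it is not, the check will need confirmation from the technician who delivers the stimulation, and the side should be noted from now on.

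The cost is one phrase and one check. An amendment through the Ethics Committee, and a report of off-site stimulation in the results, are needed only if the approved protocol or actual practice used P4 regardless of lesion side. The planned analysis and the sample size do not change.

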##### Robot-assisted therapy procedure

The RAT training will consist of 30-min exercises miming reaching and grasping movements of the UL. To perform the training, it will use the Armeo® Power II (Hocoma), an integrative system composed of a robotic exoskeleton device connected to a laptop for audio-visual biofeedback. The robotic exoskeleton, used for the therapy, is composed of an orthosis for the UL with six degrees of freedom: three for the shoulder, one for the elbow flexion, one for the forearm supination and one for the wrist flexion. Each joint is powered by a motor and equipped with two angle sensors. The device can support the patient’s UL weight, providing a feeling of fluctuation. The interface used for the exergame is designed to simulate UL gestures, providing a simple virtual environment [16]. All RAT sessions will be supervised by a specialised physical therapist with experience in the field of robotic rehabilitation (Fig. 2).

**Fig. 2 Fig2:**
[figure not shown]
Cortico-cortical stimulation and robot-assisted training protocol

#### Criteria for discontinuing or modifying allocated interventions {11b}

There will be no special criteria for discontinuing or modifying allocated interventions.

#### Strategies to improve adherence to interventions {11c}

In the present study, all sessions will be administered by a study investigator. All sessions will be recorded and reported in an adherence note.

#### Relevant concomitant care permitted or prohibited during the trial {11d}

Participants should continue to take medications for other conditions as normal. However, if it is anticipated that the participant will need benzodiazepines, baclofen and antidepressants during the intervention phase, they will be ineligible for entry into the study. If a patient needed a treatment with botulinum toxin injection for upper limb spasticity, the treatment can be performed 4 months before trial or at the end of the study period (after follow-up) worth exclusion from the study.

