### Outcomes {12}

The primary outcome of the study is the difference between the Exp group and Ctrl group in functional mobility of the UL. It will be measured using the Fugl-Meyer Assessment Scale for Upper Extremity (FMA-UE).

Secondly, we will investigate clinical, kinematic and neurophysiological changes between the two groups using:The Box and Block Test to assess manual dexterity.The Modified Ashworth Scale to assess spasticity.Kinematics variables, recorded via inertial measurement units and motion analysis during three-reaching tasks and the Box-and-Block test, to assess functional movements.TMS-evoked potentials, recorded via TMS-EEG, to assess cortical reactivity.TRSP, recorded via TMS-EEG, to assess oscillatory dynamics of the PPC and M1.PLV, recorded via TMS-EEG, to assess the actual connectivity between a targeted area with respect to the entire neural network.

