#### Methods in analysis to handle protocol non-adherence and any statistical methods to handle missing data {20c}

Handling of missing data will be performed with multiple imputation. Namely, missing values will be replaced with a set of plausible values containing the natural variability and uncertainty of the right values.

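### Section {11d} most naturally reads as excluding randomised patients who receive botulinum toxin before follow-up ends, an outcome-related exclusion that imputation alone does not repair

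*Protocol article*

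**What the plan says.** Five places in the protocol article bear on this point.

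- **Concomitant care {11d}.** The rule opens with "If a patient needed a treatment with botulinum toxin injection for upper limb spasticity" and then gives two permitted times: four months before the trial, or "at the end of the study period (after follow-up) worth exclusion from the study". For benzodiazepines, baclofen and antidepressants, the same section speaks of ineligibility for entry instead.
- **Eligibility {10}.** The entry exclusions already include "treatment with benzodiazepines, baclofen, antidepressants and botulinum toxin".
- **Discontinuation {11b}.** "There will be no special criteria for discontinuing or modifying allocated interventions".
- **Outcomes {12}.** The primary outcome is FMA-UE. The secondary outcomes include "The Modified Ashworth Scale to assess spasticity".
- **Non-adherence and missing data {20c}.** The heading covers both subjects, but the text deals with one: "Handling of missing data will be performed with multiple imputation". The only other sentence explains what imputation is.

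Section {26b} adds that patients who drop out are asked whether data already acquired may be used. No section says whether a patient excluded under {11d} is still assessed at T1 or T2.

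**The concern.** An injection given between randomisation and the end of follow-up is a post-randomisation event. Its reason, upper-limb spasticity, is what the Modified Ashworth Scale measures, and it concerns the same limb as FMA-UE. If such a patient leaves the study, the loss may depend on how the patient fares, and that may depend on the allocated treatment. Blinding limits injection decisions driven by knowledge of allocation. It does not prevent unequal exclusions that arise because one treatment truly affects spasticity more than the other.

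The non-adherence section does not settle what follows. If the patient is dropped, the comparison is no longer the randomised one. If later values are imputed, a standard imputation model assumes that the observed data explain the loss, and it borrows from patients who were not injected. That helps if T1 was recorded and already shows the decline. It does not help if the decline came after the last assessment. With 32 patients planned, each one counts.

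**Working it through.** **Reading the text.** Three features favour exclusion during the study over a pure entry condition.

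1. The section is about care during the trial, and the closed period runs to the end of follow-up.
2. Within {11d}, the other drugs make a patient ineligible for entry, while botulinum toxin leads to exclusion from the study.
3. Botulinum toxin is already an entry exclusion in {10}. If {11d} governed entry only, the reference to follow-up would have little purpose.

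**The plan's own figure.** Section {14} gives 32 patients at 80% power and 95% confidence, with no effect size or SD, so 32 cannot be reproduced. It can be back-solved, assuming 16 per arm and two-sided 5%:

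- Normal approximation: d = (1.96 + 0.84) × √(2/16) = 2.80 × 0.354 = 0.99 SD.
- t-test: d = 1.02 SD.

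The second value serves below only as a yardstick.

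**Illustration of bias.** The documents give no expected number of injections. Assume that k = 1, 2 or 3 patients are excluded, all from one arm of 16, with no true treatment effect. If the removed patients lie on average s SD below the arm mean, the mean of the rest shifts by

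shift = k × s / (16 − k).

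Simulation (100,000 trials per row, two-sample t-test at 5%) gave:

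| k | Link between exclusion and outcome | Shift (SD) | Share of 1.02 SD | Type I error |
|---|---|---|---|---|
| 1 | correlation 0.5 | 0.058 | 6% | 5.5% |
| 2 | correlation 0.5 | 0.109 | 11% | 6.1% |
| 3 | correlation 0.5 | 0.155 | 15% | 7.2% |
| 1 | worst patient removed | 0.118 | 12% | 6.9% |
| 2 | two worst removed | 0.219 | 21% | 10.6% |
| 3 | three worst removed | 0.311 | 30% | 15.4% |

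The last three rows are an upper bound. Solving the formula for s shows the deficit that they imply:

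- k = 1: 0.118 × 15 / 1 = 1.77 SD
- k = 2: 0.219 × 14 / 2 = 1.53 SD
- k = 3: 0.311 × 13 / 3 = 1.35 SD

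An assumed deficit of 1.5 SD for three patients would give 3 × 1.5 / 13 = 0.35 SD. That is more than expected even when the three worst of 16 are removed, so it should not be used.

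**Illustration of lost precision.** Against d = 1.02, losing one, two or three patients in each arm lowers power from 80% to 77%, 74% or 71%.

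**The case against.** The strongest reply is that {11d} never mentions randomised patients. The preceding sentence concerns entry, four months before the trial is a washout period, and the awkward English can be read as scheduling advice: have the injection well before, or wait until after follow-up. This reading is possible, but it explains the reference to follow-up and the change of wording less well. If it is what was meant, the sentence still needs rewriting.

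Second, a reader might infer that excluded patients are removed from the analysis. The documents do not say so. Leaving the study is not the same as leaving the analysis set, {26b} allows use of acquired data with the patient's agreement, and imputation is compatible with keeping everyone in. An analysis-set definition may also stand in a full protocol or SAP that is not shown, so its absence here is no finding. The point rests on the exclusion that is written and on what {20c} says. A later definition of the analysis set cannot recover T1 or T2 assessments that were never made.

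Third, a reader might infer that patients are removed because spasticity worsened. The text says only that treatment was needed. These are chronic patients more than 180 days after stroke, treated patients are screened out at entry, and the study lasts about 7 weeks. Exclusions may therefore be few. This stands, and it limits the size of the concern.

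Fourth, analysing values after an injection as observed is one legitimate target, and imputing as if no injection had been given is another. This also stands, and is why the fix includes a sensitivity analysis.

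**Conclusion.** The concern holds in a limited form. The most natural reading of {11d} is a post-randomisation exclusion whose trigger is related to a secondary outcome and possibly to the primary one. It is not reconciled with {11b}, and {20c} answers it only with imputation. The two sections do not flatly contradict each other, since {11b} speaks of the allocated interventions and {11d} of being in the study. Together they leave open what happens to such a patient.

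The size is unknown. The range of 0.06 to 0.16 SD, with an upper bound of 0.12 to 0.31 SD, rests on three assumptions: 1:1 allocation, 1 to 3 exclusions, and all of them in one arm. The documents support none of the three directly. The range shows what could happen in a trial of this size and is no forecast. The change is worth making because it is cheap and because assessments not collected cannot be restored later.

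**What to change.** Leave the clinical restriction on botulinum toxin as it is, and change the following.

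1. **{11b} and {11d}.** Reconcile the two, and say whether the {11d} rule applies at entry, after randomisation or both. State that a randomised patient who receives botulinum toxin before the end of follow-up is recorded as a protocol deviation, is still assessed at T1 and T2, and is analysed in the allocated arm.
2. **{20c}.** Limit multiple imputation to assessments actually missed. Add a sensitivity analysis that sets aside, or imputes, values recorded after prohibited treatment.

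The cost is a few sentences in an amendment, the assessment visits of any such patients, and one extra analysis. There is a small downside: values observed after an injection, the Modified Ashworth Scale in particular, reflect the injection as well as the allocated treatment. The sensitivity analysis shows how much this matters.
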